### Power and sample size justification

The sample size, in particular the number of sites, was determined by power analysis for a mixed model design using Optimal Design software [39]. The number of sites was selected to provide 80 % power to detect an effect of either intervention with effect size *d* of .48 compared to the effect of the control treatment. This is the effect size on intention to use hearing conservation strategies we found in our preliminary study and is just under what Cohen defined as a medium sized effect. Other necessary inputs into Optimal Design were ranges of the average number of students per site and estimates of the intraclass correlation coefficient (ICC), a measure of the tendency of individuals in the same site to have similar (correlated) responses. To determine the number of sites needed, we examined numbers of site ranging from 20 to 80, and a value of the ICC of .10 (which is typical of its value in health education intervention research [40]. We also adjusted for the possibility of 20 % missing posttest data (which we did by reducing the number of individuals per site by that percentage: thus actually testing the number of individuals per site from 16 to 64). These last adjustments increased the number of clusters we needed to include. The result of the power analysis was 80 % power to detect the target effect size with alpha of .05 two tailed if we included 36 sites with an average 16 individuals per site. Thus we have designed the study to include 36 sites (divided equally among the 3 treatments). Assuming each site includes more than 16 individuals, we will have more than 80 % power. Target youth enrollment of 576 is based on these calculations and US Agriculture Census data [41]. Enrollment numbers also include coordinators (n = 36) and instructors (n = 24).

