### Statistical analysis

Survey data will be stored on the password-protected, user-authenticated encrypted computer hard drive. Before conducting analyses to address the aims, preliminary analyses will be conducted to evaluate the quality of data and to fix illegal values.

*Aim 1 will compare effectiveness of two interventions* (community-based interactive youth educational program and community-based interactive youth educational program plus Internet booster) *to the no-intervention control treatment.* A secondary component of Aim 1 is to compare two interactive hearing interventions on youth.

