The primary measure to assess effectiveness is the 6 item scale of intention to use hearing conservation strategies (including turning down the volume, moving away from the noise, and using hearing protection devices such as ear plugs). The knowledge scale and the scale of interpersonal influences will also be examined. All individuals will be asked to assess these measures before intervention (baseline), and at 3 months and 12 months after the intervention. Since the cluster randomized design will be used to assign interventions and repeated measurements will be collected from the same individuals, linear mixed effects model will be used to investigate the effect of the interventions. The outcome variable is the scale of intention to use hearing conservation strategies. The important/main fixed effect is a categorical variable identifying the type of interventions. In addition, demographics variables will be included in the mixed model as fixed effects to increase the precision of estimates. The random effect in the model is the *site* variable. More precisely, we will use random intercept model for the *site* variable. We assume the site variable follows a normal distribution with mean zero and is independent to the error terms in the mixed model. The hypothesis is that there will be a significant effect of hearing intervention on the use of hearing conservation strategies and the intervention group will have higher use of hearing conservation strategies than the control group. If the effect of intervention is significant, follow up descriptive statistics on mean intent by time by treatment group will allow us to describe the effects, for example to determine whether each treatment led to more improvement in intent to use than the control condition and how big those effects were. Further tests within this analysis will compare the effects of the two interactive hearing interventions on youth.

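### Aim 1 tests only the overall three-arm effect and leaves each program's comparison with control, which the trial is powered for, to descriptive means

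*Protocol article*

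**What the plan says.** All places are in the protocol article.

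- *Power and sample size justification*: the number of sites is chosen for 80% "power to detect an effect of either intervention with effect size" .48 relative to control, at two-sided .05, with 36 sites split equally over three arms, 16 youth per site and an ICC of .10.
- *Statistical analysis*, opening: "Aim 1 will compare effectiveness of two interventions" with the no-intervention control. Comparing the two programs with each other is called a secondary component.
- *Statistical analysis*, model: "The important/main fixed effect is a categorical variable identifying the type of interventions". The model has a random site intercept and demographic covariates.
- Same paragraph, follow-up: "If the effect of intervention is significant, follow up descriptive statistics on mean intent by time by treatment group will allow us to describe" results. Their stated purpose is "to determine whether each treatment led to more improvement in intent to use than the control condition and how big those effects were".
- Same paragraph, last sentence: "Further tests within this analysis will compare the effects of the two interactive hearing interventions on youth".
- *Interventions*: Group B receives the same lesson as Group A. The Internet booster is added only after the 3-month survey.

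**The concern.** A significant test of a three-level factor shows only that the arms are not all equal. It does not show which program differs from control, and the direction of a difference in means carries no error rate. Yet the article gives the verdict on each program to those means. The secondary contrast (B vs A) gets a formal test; the two primary contrasts, for which the trial was sized, do not.

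This matters because the trial is meant to say which program works. Under Aim 2 the cost-effectiveness ratio is calculated once effectiveness is significant, and under Dissemination the move to full-scale Safety Day delivery depends on satisfactory effectiveness. The case most exposed is a lesson whose effect has faded by 12 months beside a lesson plus booster that still works. The overall test would then be carried by B, and A could be reported as better than control on the sign of a chance difference.

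**Working it through.** **Inputs** (Power and sample size justification): 12 sites per arm, 16 youth per site, ICC .10, d = .48, two-sided .05.

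**1. The plan's own power figure.** In SD units:
- Variance of a site mean = .10 + .90/16 = .15625.
- Standard error of a difference between two arms = sqrt(2 × .15625/12) = .1614.
- Noncentrality = .48/.1614 = 2.97.
- Power from the noncentral t with 22 df = 81.1%. Eleven sites per arm would give 77.3%.

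So the stated 80% is the power of one unadjusted comparison of a program with control.

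**2. The written rule, one follow-up score.** Site means were simulated (1,000,000 trials per case). The overall F test on 2 and 33 df was taken at .05, and a program was counted as better than control if the test was significant and its mean lay above control.

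| True effects (A, B; control 0) | Overall test significant | A's mean above control as well |
|---|---|---|
| 0, .48 | 84.4% | 42.2% |
| 0, 0 | 5.0% | 2.5% |
| .48, .48 | 84.4% | 84.4% (correct) |

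In the first row the result is the power of the overall test times one half: .844 × .5 = .422. It therefore moves with that power: 22% if the working program has d = .30 and 48% if d = .60; 32% at ICC .20 and 47% at ICC .05.

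**3. The same rule, both follow-ups averaged.** If A is null, B is also null at 3 months, because the booster comes later. An effect of .48 at 12 months only averages (0 + .48)/2 = .24. The within-person residual correlation r between the two surveys is not given, so r is an assumption, taken from 0 to 1:
- Site-mean variance = .10 + .90 × (1 + r)/(2 × 16), which is .128 at r = 0 and .156 at r = 1.
- Overall test significant: 34.8% (r = 0) to 29.2% (r = 1).
- Significant with A's mean above control: 17.4% to 14.6%.

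**4. A tested contrast in place of the means.** If A vs C is tested at two-sided .05 only after a significant overall test, a null A is declared better than control in 2.5% of trials in the setting of step 2 and about 2% in that of step 3.

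**5. Power per contrast under a formal rule** (12 sites per arm, 16 per site, ICC .10, d = .48, one score): 78% when gated by the overall test; 74% with Dunnett (critical |t| about 2.31); 73% with Holm.

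**The case against.** - **The design does not fit the 42% case well.** A reader might take 42% as the error rate of the plan. The documents do not support that. The model uses repeated measurements and B differs from A only after 3 months, so 42% belongs to a single follow-up score such as 12 months. Averaging both follow-ups gives 15-17%, and letting baseline rows enter the arm effect as well would bring it to 8-9%. This part of the objection stands.
- **Any positive difference is counted.** The article also mentions the size of the effects. In the single-score case, requiring an observed A-C difference above .10 SD leaves 23%, and above .24 SD (half the planning effect) about 6%. The article states no such threshold, so this softens the figure without removing the gap.
- **The B vs A test offers some protection.** In the 42% of trials, B beats A at two-sided .05 in about 85%, so A would seldom look equal to B. That still does not answer whether A beats control.
- **The planning premise is that both programs work.** Then the means point the right way in essentially every significant trial. True, but the trial is run to find out.
- **It is detail for the analysis plan.** Silence would be. Here the article itself assigns the decision to descriptive statistics.

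Two further inferences fail. The singular in "the intervention group will have higher use of hearing conservation strategies than the control group" might suggest a competing test of the pooled programs against control; no such test is proposed anywhere, and the other sections speak of each intervention. Nor does the plan propose ungated pairwise tests against control, so it cannot be charged with their family-wise inflation.

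**Conclusion.** The point holds. The contrasts on which Aim 1 is framed and powered have no test or error control, and the article puts descriptive means in their place. The overall test itself is valid at 5%; the weakness lies in the statements about each program.

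The size depends on the truth and on which follow-up the arm effect represents. With one program null and the other at d = .48, the null program is read as better than control in about 42% of trials on a single follow-up score, and in about 15-17% when B's effect is confined to 12 months and both follow-ups are averaged. If neither works it is 2.5% for a given program; if both work there is essentially no error. These figures rest on the plan's inputs, on site-mean analyses without covariates, and on reading more improvement as a higher mean.

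**What to change.** In the Aim 1 paragraph of Statistical analysis, replace the descriptive follow-up with two contrasts on intention, A vs C and B vs C, estimated from the same mixed model and arm effect as the overall test. Give each an estimate, 95% CI and p-value. Choose one rule:

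- Test each contrast at two-sided .05 only if the overall test is significant. With three arms this controls the family at .05: if all arms are equal the gate holds the error, and if only two are equal just one true null remains to be tested.
- Or use Dunnett or Holm for the two contrasts.

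Keep B vs A secondary, and word the hypothesis as each intervention versus control. In Power and sample size justification, restate power for the chosen rule: about 78% per contrast when gated, or about 74% with Dunnett, against the 80% stated for one unadjusted contrast.

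No new data or participants are needed. The only cost is the slightly lower stated power.

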#### Aim 2 will compare program costs

Costs in dollars (e.g., material, travel) will be summarized using mean and standard deviation for each site. Costs in time from volunteers and students will be summarized using mean for each site. At site level, the difference in cost between three intervention groups are compared using one-way analysis of variance. If the effectiveness of intervention is significant, the costs to effective ratio will be calculated to quantify incremental cost of effectiveness.

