**Methods:**

The purpose of this project is to test innovative hearing health education programs delivered to a large target group and to determine the effectiveness and sustainability of these programs in promoting hearing health among farm and rural youth. Specifically, this project includes: a) an interactive face-to-face informational program alone, b) an interactive face-to-face informational program followed by an Internet-based booster, and c) a no-intervention control. Sites will include selected affiliates of a major farm youth safety education organization. Data will be collected at baseline, 3, and 12 months. A linear mixed model will be used to compare the effectiveness of the three interventions over time. Descriptive statistics will be used to compare program costs and sustainability ratings.

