Intervention B consists of an Internet-based educational booster. The Internet-based booster reinforces Intervention A content through use of the Dangerous Decibels® virtual exhibit (DDVE), an existing online educational program consisting of eight activities (www.dangerousdecibels.org/exhibit/virtual-exhibit/). The booster is developmentally appropriate, focuses on sources of sounds, consequences of noise exposure, and prevention of hearing loss. In a study testing the effectiveness of the DDVE site when used alone, students showed improvement in knowledge immediately after the intervention, although improvements were not sustained after 3 months. The Internet-based booster is a user-driven activity where students explore a variety of learning activities at their own pace. Highly interactive game-based activities include rating noise sources (e.g., lawn mower) as safe or dangerous, determining the best course of action (i.e., turn it down, walk away, wear hearing protection) in a variety of noisy situations, and choosing a course of action when confronted with social non-support of use of hearing protection. A computer (with Macromedia Flash® and Shockwave®) and Internet connection (e.g., at home, school, or public library) is required for participation.

The study design includes three arms: an interactive a face-to-face Safety Day lesson alone (Group A), a face-to-face interactive lesson followed by an Internet-based booster (Group B), and a no-invention control (Group C, Fig. 2). The Internet booster will be delivered to eligible participants following completion of the three month survey.

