#### Intervention effectiveness evaluation

After obtaining parental informed consent and soliciting the assent of child participants, pre- and post-intervention data will be collected from youths. Pre-test data will be collected via pencil-and-paper survey forms prior to the delivery of content. Three- and 12-month post-test data will be collected via the youth’s preferred communication medium following the booster intervention. Instrument means, standard deviations, and alpha coefficients are summarized in Table 2.

**Table 2 Tab2:** Timetable of project activities and benchmarks for success

Activity	Year 1 months						Year 2 months						Year 3 months						Year 4 months		
	1/2	3/4	5/6	7/8	9/10	11/12	13/14	15/16	17/18	19/20	21/22	23/24	25/26	27/28	29/30	31/32	33/34	35/36	37/38	39/40	41/42
Recruit, enroll & randomize 36 sites	X	X	X	X																	
Train coordinators (Groups A,B); & distribute materials (Groups A,B,C)		X	X	X	X	X															
Recruit 24 instructors; enroll youth; collect baseline data; deliver interactive program (Groups A,B)					X	X	X	X													
Distribute, collect 3-month surveys (Groups A,B)					X	X	X	X	X	X											
Distribute booster reminders (Group B)							X	X	X	X	X	X									
Collect 12-month surveys; distribute incentives (Groups A,B,C)											X	X	X	X	X	X					
Complete sustainability assessment														X							
Analyze data															X	X	X				
Submit progress reports						X						X						X			X
Disseminate & submit manuscripts																			X	X	X

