#### Cost

The cost of implementing the program will be based on data associated with program personnel, instructional materials, and travel incurred with the educational process.Personnel (coordinators, instructors, youth): We will estimate hearing education program personnel costs beyond those already incurred through previously established Safety Day programs, i.e., youth, coordinator, and instructor time.Instructional materials: We will value all materials used to implement the lesson (e.g., sound meters, printed supplies), including lesson development costs and youth time on public-access or home-based computers.Travel: We will estimate travel costs incurred by coordinators, instructors, and youth to participate in pre-program training and the local Safety Day program.

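### Aim 2 calculates the cost-effectiveness ratio only after a significant effect, and tests cost by a three-arm ANOVA that cannot show whether B costs more than A

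*Protocol article*

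**What the plan says.** Aim 2 in the Statistical analysis section fixes two rules. The first is the cost test: "At site level, the difference in cost between three intervention groups are compared using one-way analysis of variance". The second is the condition on the ratio: "If the effectiveness of intervention is significant, the costs to effective ratio will be calculated to quantify incremental cost of effectiveness". Site-level cost summaries are reported in any case.

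The Cost section defines what is counted:

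- **Personnel** is incremental: "We will estimate hearing education program personnel costs beyond those already incurred through previously established Safety Day programs".
- **Materials** are tied to the lesson: "We will value all materials used to implement the lesson".
- **Travel** is not limited to the increment: "We will estimate travel costs incurred by coordinators, instructors, and youth to participate in pre-program training and the local Safety Day program".

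The Interventions section lists the third arm as "and a no-invention control (Group C, Fig. 2" (a misprint for no-intervention). The project timetable (Table 2) has the row "Train coordinators (Groups A,B); & distribute materials (Groups A,B,C", so coordinator training is confined to A and B while some materials also go to C.

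The abstract describes the cost comparison differently: "Descriptive statistics will be used to compare program costs and sustainability ratings".

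**The concern.** Two separate rules are at issue.

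**The condition on the ratio.** If the ratio is calculated only when the effect is significant, the trials that report one are those in which the effect estimate happened to be high. The effect is the denominator, so the reported ratio is on average too favourable to the program. When the effect misses significance no ratio is planned, although the Discussion presents finding the most cost-effective approach as a purpose of the trial.

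**The three-arm cost test.** Sites without the lesson should have almost nothing to record under incremental personnel time and lesson materials. On those items the overall F test mainly asks whether a program costs more than no program. The question a program manager would put is what the booster adds to the cost of the lesson, and the overall test does not answer it. Aim 3 has the same structure and compares only A with B.

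**Working it through.** **Inputs from the article (Power and sample size justification).** 36 sites in three equal arms, so 12 per arm; average 16 youths per site; ICC 0.10; d = 0.48; two-sided alpha 0.05. No cost figures are given, so all cost means and coefficients of variation (CVs) below are assumptions.

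**1. The plan's own figure.** In SD units, the variance of a site mean is 0.10 + 0.90/16 = 0.15625. For one intervention against control there are 24 sites, and the noncentrality is 24 × 0.48² / (4 × 0.15625) = 8.85. With F(1, 22), power is 0.811, which agrees with the stated 80%. The standard error of the difference is √(0.15625 × 2/12) = 0.161.

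**2. The condition on the ratio.** The article does not say which test must be significant, so three versions were evaluated, with both interventions at the same d:

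- *Pairwise test, intervention against control:* 22 df.
- *Overall three-arm F test on site means:* noncentrality 12 × (2d²/3) / 0.15625 = 8d²/0.15625, which is 11.80 at d = 0.48 and 4.61 at d = 0.30, with F(2, 33).
- *Overall Wald chi-square:* the same noncentrality, 2 df, variance taken as known.

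| Gate | d | Ratio calculated | No ratio | Mean effect when significant ÷ true effect |
|---|---|---|---|---|
| Pairwise | 0.48 | 82% | 18% | 1.11 |
| Overall F | 0.48 | 84% | 16% | 1.08 |
| Overall Wald | 0.48 | 88% | 12% | 1.07 |
| Pairwise | 0.30 | 42% | 58% | 1.51 |
| Overall F | 0.30 | 43% | 57% | 1.38 |
| Overall Wald | 0.30 | 47% | 53% | 1.37 |

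The pairwise rows use normal draws with the t critical value. With the variance estimated as well, they become 81% and 1.11 at d = 0.48, and 43% and 1.47 at d = 0.30. Under the pairwise gate, with cost held fixed, the median reported ratio is 0.93 of the true ratio at d = 0.48 and 0.70 at d = 0.30.

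**3. The three-arm ANOVA.** 20,000 simulated trials per setting, 12 sites per arm, gamma-distributed site costs, A and B both with mean 100. Where C is not zero, its CV is 0.5.

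| Mean cost in C | F test significant although A = B (site CV in A and B from 0.3 to 1.0) |
|---|---|
| 0 | 100% to 98.6% |
| 10 | 100% to 95% |
| 50 | 99% to 23% |

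With C near zero the result is known in advance and carries no information on B against A. With C at half of A's cost, for example because ordinary Safety Day travel is counted, it is no longer a foregone result. A direct Welch test of A against B, with C at zero, rejects in 4.1% to 4.6% of runs when the two cost the same.

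**4. Which cost items apply to C.** Personnel is defined beyond existing Safety Day costs, and materials are those of the lesson. Table 2 recruits 24 instructors, which matches 2 × 12 lesson sites. These items point to near zero in C. Travel points the other way, because youths and coordinators travel to Safety Day in every arm.

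**The case against.** **Control cost.** A reader might infer that C's cost is zero by definition. The article does not say so. Travel to the local Safety Day is counted without an incremental limit, and some materials go to Group C, though these may be survey forms. This stands: the near-certain F test applies to the personnel and lesson-material items, not necessarily to total cost.

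**Type I error.** A reader might also charge the plan with an inflated error for B against A. If C had no variance, the pooled error would be (11s² + 11s² + 0)/33 = (2/3)s², and an unadjusted contrast using it would reject in about 11% of trials when A and B cost the same. But the article names no follow-up contrast, and a Tukey comparison would give about 5.8%. The 11% is a risk of one possible choice, not a property of the plan.

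**Misleading or merely uninformative.** An overall test with a predictable answer misleads only if it is read as a comparison of B with A. This also stands.

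**Size of the selection.** At the design effect the overstatement is modest, and d = 0.30 is not a value from the article. Costs and effects would still be reported separately, so a reader could form a ratio unaided. That weakens any claim that the cost-effectiveness answer is lost altogether. It does not justify a rule under which the trial's own ratio, with its uncertainty, appears only when the result is favourable.

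**Conclusion.** The concern holds in a limited form. The condition on the ratio is a real flaw that does not depend on what Group C costs. At d = 0.48, with 16 youths analysed per site and ICC 0.10, it overstates the effect about 1.07- to 1.11-fold and leaves no ratio in roughly 12% to 18% of trials. If the true d were 0.30, this becomes about 1.4- to 1.5-fold and more than half of trials. The ranges reflect the article's silence on which test is the gate.

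The three-arm ANOVA is a poor choice for the personnel and lesson-material items, where it is almost certain to be significant and does not separate B from A. For a total that includes Safety Day travel this is less certain, and the size depends on assumed costs.

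The abstract and Aim 2 disagree on whether the cost comparison is descriptive or a test. None of this touches the primary effectiveness analysis.

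**What to change.** - Report incremental cost, incremental effect and their ratio for A against C, B against C and B against A, each with a site-level bootstrap interval, whatever the p-value.
- Replace the three-arm ANOVA with a direct site-level comparison of cost, B minus A, by a method that allows unequal variances and skew (Welch or bootstrap).
- Exclude ordinary Safety Day travel, so that travel follows the same incremental rule as personnel.
- Reconcile the abstract with Aim 2.

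The cost is a change of analysis wording and a bootstrap; no extra sites or participants are needed. The drawback is that the interval for the ratio may be wide or undefined if the effect is near zero, and this would have to be reported as such.
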